## Abstract

**Background:**

Recent studies show adolescent health-related behaviours to co-occur synergistically. This paper describes the study design for an exploratory trial on the effects of a comprehensive, whole-school health promoting school intervention. This intervention tackles seven different behavioural domains simultaneously via a combination of education, creating a healthy environment and introducing healthy behavioural policies. Additionally, extensive partnerships are formed between schools, parents, neighbourhoods and youth health authorities to coordinate health promotion efforts.

**Study design and data collection methods:**

The intervention will be implemented at two secondary schools. Results will be compared with two control schools (n≈1500). The intervention’s effectiveness in changing student behaviours as well as physical and psychosocial health status along with qualitative lessons learned on the integration of youth health care services and school health education practices are the main aimed outcomes of this study. Data are collected via a mixed methods design combining an annual youth health (behaviour) monitor with a qualitative process evaluation via interviews with key stakeholders.

**Data analysis:**

A multilevel analysis is performed combined with a systematic analysis of qualitative interview data.

**Conclusions:**

This study will produce an evaluation of a comprehensive health promoting school intervention that combines an integrated approach of schools, neighbourhoods, families and youth health services to improve adolescent health.

## Introduction

Unhealthy behaviours such as alcohol use, smoking, unhealthy nutrition or excessive time spent behind screens (e.g. the television, computer or game console) show alarming trends in The Netherlands and the rest of the developed world [1, 2]. Children and adolescents are a particularly vulnerable subpopulation in this respect, with half of all adolescents being involved in *at least* one or more unhealthy behaviours [3]. Many of these unhealthy behaviours are known to originate in adolescence and consequently pose a gateway to poor adult health [4]. Moreover, recent literature suggests that these behaviours act as being associated with each other instead of acting independently. In several recent studies this clustering is hypothesized to act on one’s health interactively, i.e. individual behaviours yield greater effects when present together than their individual sums would be expected to [1, 5–8].

Therefore, research increasingly suggests that multi-behavioural targeting interventions hold the most promising future perspectives when it comes to influencing unhealthy behaviours via preventive action [7–10]. It is suggested that these interventions hold the advantage of also simultaneously influencing behaviours outside primarily targeted ones; for example, intervening in adolescents’ smoking behaviour, while then simultaneously also affecting their alcohol consuming behaviour. Several recent studies have shown promising examples of this principle and they show interesting developments for their practical implications [7, 8, 11]. However, unfortunately, most empirical intervention studies still focus on targeting one single risk factor or behaviour at a time, which often causes failure to take into account much of the real world relevance that is crucial to gaining valuable insights into evaluating such interventions in a real-life educational setting [9, 12–15]. They do not sufficiently assess the intervention’s effects in a comprehensive fashion. Therefore, several recent papers of different types of studies, such as those by James Prochaska [10], Judith Prochaska et al. [13, 16–19] and Alfredo Morabia and Costanza [20, 21], have recently pressed the importance of persisting to study health (interventions) in real world settings to achieve the needed *meaningful* progress in (school) health promotion research. Also among them are several (trial) studies by Brian Flay [22–24], who states that: “*problem/risky behaviours, unhealthy behaviours, anti-social behaviour, poor mental health, and poor academic achievement should be addressed by a comprehensive, coherent, and integrated approach, rather that the disjointed approach to prevention and promotion taken by education today*” [22, p. 4]*.*

### Pilot study

In 2006 a health promoting school pilot was developed and implemented on a secondary school in The Netherlands (see Figure 1). It targeted young adolescents of the first three grades of a Dutch secondary school (approx. 11–16 year olds). The desire to pursue a more comprehensive, evidence-based health promoting school concept drove the development of this pilot; a desire that originated due to persistent complaints from parental and teachers’ about the students’ unhealthy lifestyle. These complaints were a result of persisting problems with, among other things, students’ (extreme) alcohol use and bullying. Therefore, this particular group of young adolescents was chosen as target population for this pilot, although the authors realize that much progressive research has been performed on intervening in younger children by pioneers in the field, such as Lawrence St. Leger [25].

The pilot was inspired by the *Schools for Health in Europe*’s (SHE)* Whole School Approach (WSA)* [26–28]. This model promotes a comprehensive *total-life-approach* instead of focusing on a single dimension of child health, such as school life or family life. Following the WSA’s framework, the pilot consisted of several components [29]. First, several evidence-based curricular components were *integrated* into the pre-existing curriculum, instead of simply replacing or adding to it. These curricular changes brought about that: 1) health education constituted a significantly larger portion of the school’s curriculum targeting several topics more in-depth than is common in Dutch secondary schools, 2) health education topics were structurally embedded into the curriculum, instead of being disjointed, sporadic projects, 3) certain topics were targeted in a clustered fashion, such as substance use behaviours or screen time behaviours, 4) evidence-based methods were used in health education, which is also uncommon practice in Dutch secondary schools, 5) a strong focus was placed on students’ personal skill development, refusal skills training, peer education and genuine, active participation [30], and 6) annual monitoring of student health behaviours and health status took place via a self-report questionnaire to fine-tune school policy and create annual spear points.

In total, seven health related behaviours were simultaneously targeted in the pilot, selected based on academic literature, namely nutrition, physical exercise, substance use (alcohol and marijuana), smoking, bullying, sexual behaviour and screen time behaviours [watching television, pc/internet use and (online) gaming]. The most notable ‘newcomers’ in this group of behaviours are the *screen time behaviours*. They were chosen due to their addictive potential and their importance to both physical and psychosocial adolescent health, as stated in recent studies [31].

In addition to the curriculum changes, different (health) behavioural school policies (e.g. no smoking policy) were implemented, together with the creation of a healthy, supportive school environment (e.g. no candy machines at school, a healthy school canteen). Also, extensive partnerships with the students’ social environment (with parents, the local police, local supermarkets, etc.) were formed to facilitate the development of a healthy environment for the students outside of school. In addition, the municipal health services were re-oriented towards school and prevention by e.g. creating a faster referral service to local primary health care services. Therefore, the municipal health services form close partnerships with the school to be involved with the format and content of the pilot in order to fine-tune it to recent evidence-based or best practices.

### Implementation of the pilot on the school

Instead of standardizing the pilot, the school adopted a tailored, school-specific implementation approach, based on theory and literature. To achieve this, the school first prioritized what health-related behaviours and topics a health promoting school should focus on by applying a baseline student-questionnaire/monitor to map all relevant behaviours and issues. Afterwards, these outcomes were discussed with the parents, via the parent council, in order to place emphasis on appropriate topics and to initialize the process of installing a health promoting school steering group to guide the prioritizing and further implementation. This steering group consisted of a representative of the student council, the parent council, of the teaching staff, of the school board, of the school policy makers and several researchers and policy-makers from Dutch knowledge/academic institutes and the regional public health authorities. The ‘academic’ participants were involved to ensure the evidence-based nature of the incorporated materials/intervention parts, while the ‘school’ participants were responsible for the tailoring of these materials/intervention parts to fit the specific school context.

### First results of the pilot study

Recently, several papers have been published about the pilot study and student behaviours on the school [11, 32]. First, De Leeuw and colleagues reported on the (online) gaming and internet/pc use behaviours [11]. In addition, Sterkenburg and colleagues recently described the relationship between bullying, psychosocial health and happiness at the school [32]. Furthermore, other preliminary results suggest positive effects with regard to smoking, alcohol use, binge drinking and cannabis use.

### Lessons learned during the pilot study

The pilot study’s most notable lessons learned mainly regarded the novel multi-actor nature of the intervention, involving school, parents, neighbourhood and municipal health services. It was shown to be important to 1) assess the feasibility of close cooperation with the students’ parents, 2) to facilitate a close cooperation with the municipal/regional health services in order to keep the educational modules and methods evidence-based and up to date, 3) fine-tune initiatives within the school’s neighbourhood (e.g. surrounding supermarkets), and 4) to provide the teaching staff with in-service trainings, in order to provide them with the necessary tools and competencies to optimally function in this ‘new’ curriculum and context. During the pilot study, the municipal health services showed great willingness to provide schools with such help e.g. by means of delivering evidence-based educational materials and teacher in-service trainings. All these partnerships facilitated an integral, more intensified approach to local health promotion, through integration of school, local environments and primary health care services.

After viewing the positive effects of the pilot on the school, the current, follow-up study was initiated to determine the feasibility of the intervention at more regular secondary schools with more ‘standard’ student demographics and school conditions. This study protocol presents the rationale and methodology for the exploratory trial study [33] of the pilot, named and from hereon referred to in relation to the follow-up study as the *Utrecht Healthy School (UHS)*.

## Methods

### Study design: an exploratory trial

The UHS remains similar in terms of format, content and implementation as the pilot, only targeting different schools in a different study setting. It will be implemented on two Dutch secondary schools, with two comparable schools serving as controls (n≈1500 students) in an exploratory trial study design [33].

The main outcomes of the study will be the (health) behavioural change effects in students. In addition, the qualitative process evaluation components serve to optimally interpret the quantitative student behavioural change data in their proper context and to evaluate the UHS’ feasibility for implementation on relatively ‘standard’ schools in The Netherlands, selected as a convenience sample. Afterwards, comparable control schools were selected and incorporated in the study. Campbell et al. underscore the value of such a mixed methods approach, due to the complexity of the UHS [34]. Their model of “*continuum of evidence for complex interventions*” applies well to the current study, which resides in its Second Phase. In Phase II, the UHS study resides between a randomized controlled trial phase (Phase III) and the pilot phase (Phase I) [33]. During this phase the UHS’ effects and implementation processes are evaluated under more regular circumstances in an exploratory fashion via a small-scale, controlled intervention-control study. The main issues to take into account in such studies, according to Campbell et al. [33], are 1) ensuring a sound theoretical understanding of the problem, 2) realizing that a lack of intervention effect may reflect implementation failure rather than a genuine lack of program effectiveness, 3) the variability in individual level outcomes may reflect upon higher processes, 4) a single primary outcome may not make the best use of the data, which means that e.g. quantitative data can better be interpreted when accompanied by related qualitative data that may provide the necessary context, and 5) realizing that ensuring strict standardization may be inappropriate in this context. The UHS may work better when a certain degree of adaptation to local settings is permitted. As the model by Parsons and Stears illustrates (Figure 2), such processes are suggested to accompany the according goals of Health Promoting School interventions. During the implementation at the two intervention schools, an entire year has been spent to fine-tuning these processes. Flay also provides similar recommendations, specifically for these kinds of complex interventions, naming this phase/type of study a *prototype evaluation study* [36].

### Sample and procedures

Students from grade one to three (11–16 year olds) are questioned via an annual online questionnaire, completed individually, in-class. Survey procedures are designed to allow students to participate *voluntarily* and *confidentially*; prior to the survey students are extensively informed of this. These procedures were similar in the pilot project.

#### Student survey

The survey assesses a range of health behaviours, health outcomes and socio-demographic characteristics. Most items were derived from the validated Dutch conversion of the HBSC-survey [37, 38] (see Table 1). Non-HBSC items are the Compulsive Internet Use Scale [45] and the Videogame Addiction Test [40].

### Process evaluation

Periodic, semi-structured interviews are performed with the Healthy School Coordinator to gain insight into the (progress of the) implementation process. S/he is a central coordinating figure in each participating school. S/he forms the link between school-related health promotion activities, parents, neighbourhoods and the municipal health services. S/he assures that the SHE’s *whole-school approach* [26, 28] is followed. This level of cooperation between the education and primary health care sector on such an individual school level is uncommon in The Netherlands. Similar interviews are performed at the control schools with the central contact person to account for any changes in related curricular activities to allow for better data-interpretation. The process evaluation is thematically analyzed by means of the qualitative data analysis program NVIVO [44].

## Data analysis

### Main outcomes: student behavioural changes

Multilevel regression analyses and ANCOVA analyses will be performed to analyze changes in student health behaviours and health outcomes. The multilevel analyses will contain two levels: the school level and the individual student level.

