#### Power calculations

Prior to this exploratory trial, the means and standard deviations of the main behavioural outcomes were estimated in the pilot study, based on previous Dutch studies to perform a power analysis for determining the study’s required sample size. As stated in literature, a ‘generic’ target of 10–15% points of detectable change suits a program such as this UHS-exploratory trial [46]. As stated by Babyak, for multiple regression analyses 15 persons/observations per parameter are to be included in the measurements for conservative power calculations [47]. With an expected response rate of >90% and 30 included parameters to be measured, a sample size of approximately 500 observations is required for a power of 0.80 at an alpha-level of 0.05 for statistical significance, whilst approximately 1500 students are expected to participate in the study. The sample size thus exceeds the needed requirements, but was chosen to guarantee the study results being sufficiently representative and to allow for sub-group analyses.

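### With two schools per arm the intervention effect rests on 2 degrees of freedom; large-sample tests, or an ANCOVA that ignores school, would exceed the 0.05 level unless the school ICC is close to zero

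*Protocol article*

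**What the plan says.** Under Study design, the article describes an intervention in "two Dutch secondary schools, with two comparable schools serving as controls". Table 1 of the article codes school with four values. The intervention is delivered to whole schools, so the school code determines the arm.

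Under Main outcomes: student behavioural changes, the analysis is given in two sentences: "Multilevel regression analyses and ANCOVA analyses will be performed to analyze changes in student health behaviours and health outcomes", and "The multilevel analyses will contain two levels: the school level and the individual student level". The article does not say whether the ANCOVA accounts for school, and it names no estimator, reference distribution or degrees-of-freedom method.

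Under Power calculations, the significance level is 0.05 and adequacy is judged by counting students: "a sample size of approximately 500 observations is required for a power of 0.80 at an alpha-level of 0.05 for statistical significance", while "approximately 1500 students are expected to participate in the study". No ICC appears there or elsewhere.

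**The concern.** Adding students makes each school's mean more precise, but it adds nothing to what is known about how much schools differ for reasons unrelated to the intervention. That variation is the yardstick for the arm effect, and four schools estimate it with 2 degrees of freedom. A multilevel model contains the right variance component, but it gives valid tests only if its reference distribution reflects how poorly that component is estimated. With a normal reference it does not. With so few schools the component is also often estimated as exactly zero, and the model then treats students as independent. An ANCOVA without school does so from the start.

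At stake is the reading of a main outcome. Ordinary differences between four schools could be reported as behavioural effects, and Table 1 lists many outcomes on which this could happen.

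**Working it through.** **Inputs.** Four schools, two per arm (Study design; Table 1). About 1500 students, so m = 1500/4 = 375 per school if schools are equal in size (assumption). Alpha 0.05, taken as two-sided (assumption). ICC ρ: not given, so a range is shown. Normally distributed outcome (assumption for the simulation).

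**The article's own figure.** The Power calculations section uses 15 observations per parameter and 30 parameters: 15 × 30 = 450, and 450/0.90 = 500. This reproduces the stated 500 exactly. It is a rule about the number of regression parameters and has no term for schools.

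**Degrees of freedom.** With total variance 1, each school mean has variance ρ + (1 − ρ)/m. The arm difference is a mean of two schools minus a mean of two schools, so its variance is (1/2 + 1/2) × [ρ + (1 − ρ)/m] = ρ + (1 − ρ)/m. This is estimated from the two within-arm school differences: 4 − 2 = 2 df, critical value t(0.975; 2) = 4.303.

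**Large-ICC limits of a test at 1.96.**
- REML: P(|t₂| > 1.96) = 0.189, or 3.8 times nominal.
- ML divides the between-school sum of squares by 4 instead of 2, so the limit is P(|t₂| > 1.96/√2) = 0.300, or 6.0 times nominal.

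**Simulation.** One million null trials per ICC, 4 × 375 students, balanced random-intercept fits with the school variance truncated at zero:

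| ICC | REML, 1.96 | ML, 1.96 | ANCOVA ignoring school | t (2 df) on school means | REML variance = 0 |
|---|---|---|---|---|---|
| 0 | 4% | 5% | 5% | 5% | 63% |
| 0.001 | 6% | 8% | 10% | 5% | 52% |
| 0.003 | 10% | 14% | 18% | 5% | 37% |
| 0.005 | 12% | 18% | 25% | 5% | 29% |
| 0.01 | 15% | 23% | 37% | 5% | 19% |
| 0.02 | 17% | 27% | 50% | 5% | 11% |
| 0.05 | 18% | 29% | 66% | 5% | 5% |

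**Does a software df correction suffice?** Suppose the correction uses 2 df when the REML variance is positive and residual student-level df when it is truncated to zero (an assumption about behaviour at the boundary). Type I error is then about 7.3%, 7.3%, 6.5% and 5.6% at ICC 0.005, 0.01, 0.02 and 0.05. Applying 4.30 to the truncated REML standard error overcorrects instead: 0.4%, 1.3%, 2.6% and 4.1%. Only the untruncated school-level t test holds 5% throughout.

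**What the valid test can detect.** Take a proportion near 50% and 375 students per school. The difference detectable with 80% power is 5.65 × √{0.25 × [ρ + (1 − ρ)/375]}, where 5.65 is the non-centrality needed at 2 df. This gives about 25, 32 and 42 percentage points at ICC 0.005, 0.01 and 0.02. Power for the article's target of 10–15 points runs from 0.26 to 0.46, from 0.19 to 0.33 and from 0.13 to 0.22 respectively. At ICC 0 it runs from 0.54 to 0.82.

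**The case against.** The strongest reply is that the article never commits to a wrong test. Its two-level structure is correct, and estimator and df method are details that a condensed article commonly leaves to a full plan. That stands as far as silence goes: omitting a df method is not in itself an error. What the article does fix is the four schools, an ANCOVA beside the multilevel model, the 0.05 level, and a judgement of adequacy made from student numbers. Ordinary large-sample output would therefore give wrong error rates, and no later choice of software option creates more than 2 df.

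A reader might infer that the tests will necessarily be too liberal by a factor of two to six. The documents do not support that. They give neither ICC nor estimator. At ICC 0–0.001 the inflation is absent or slight, REML reaches a factor of two only at an ICC of about 0.003 and cannot exceed 3.8, and six is the large-ICC limit of ML alone.

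A reader might also cite the smallest two-sided permutation p-value for two versus two schools, 2/6 = 0.33. It is only illustrative, because the schools were a convenience sample with controls selected afterwards, not a random allocation.

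Two further points stand. Many Table 1 outcomes are binary, so the normal-outcome rates are a guide rather than exact. And the study is labelled exploratory, which lessens the harm of a wrong p-value but does not change the degrees of freedom.

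**Conclusion.** The point holds in conditional form. That the arm contrast has 2 df follows from the design alone. The inflation depends on the reference distribution and the ICC. With a normal or large-sample reference, type I error is about 10–18% (REML) or 14–29% (ML) for ICCs of 0.003–0.05, and 4–8% at ICCs of 0–0.001. With an ANCOVA that ignores school it is about 25% at ICC 0.005 and 37% at 0.01. These figures assume a normal outcome, equal schools of 375 students, a two-sided test and ICCs that the article does not supply; the relevant ICC is that of the outcome after baseline adjustment. The article does not show that such a test will be used, so this is a recommendation to fix the basis of inference, not proof of a stated error.

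**What to change.** In Main outcomes: student behavioural changes, state that inference about arm uses the four school-level baseline-adjusted changes, in means or, for Yes/No outcomes, proportions. Compare the arms with a 2-df t interval whose variance comes directly from the school values, without truncating the school component at zero. Baseline should be handled through the change or by student-level adjustment; regressing four school values on a school-level baseline would leave only 4 − 3 = 1 df.

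The two-level model may be kept for description, but do not rely on REML with Satterthwaite or Kenward-Roger df for the arm effect, since these can fail when the school variance is estimated as zero. Do not base arm inference on a student-level ANCOVA. Report all four school-specific changes for each outcome, and present effects as exploratory estimates with intervals rather than as claims of significance. In Power calculations, say that the 500 and 1500 count students and do not establish power 0.80 for a comparison of four schools.

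No new data are needed. The cost is wording and wider intervals: the multiplier on the standard error rises from 1.96 to 4.30, and the 10–15 point target is out of reach at 80% power for a proportion near 50% once the ICC is 0.005 or more. The 2-df interval allows for random variation between schools, but it does not remove bias from the non-random choice of schools.

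### The two-level model leaves out the school class, so standard errors will be too small for effects that vary mainly between classes (track, grade and their interaction with arm) if outcomes cluster by class

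*Protocol article*

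**What the plan says.** Under Data analysis, Main outcomes, the article names its methods: "Multilevel regression analyses and ANCOVA analyses will be performed to analyze changes in student health behaviours and health outcomes". It then sets the hierarchy: "The multilevel analyses will contain two levels: the school level and the individual student level". This is a stated model choice, not a detail left open.

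Other sections bear on it:

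- Study design: "It will be implemented on two Dutch secondary schools, with two comparable schools serving as controls". There are therefore four schools, two per arm.
- Sample and procedures: students in grades one to three "are questioned via an annual online questionnaire, completed individually, in-class".
- Pilot study: the programme works through the curriculum and includes peer education and refusal-skills training. Study design says the present intervention keeps the pilot's format and content.
- Power calculations: "approximately 1500 students are expected to participate in the study", a number chosen above the stated requirement partly "to allow for sub-group analyses". The sub-group factors are not named.
- Table 1: school has four codes, and educational track (labelled there as school level) has three levels. Class is not listed.

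**The concern.** Class is the unit in which students are taught, exposed to the programme and surveyed. Smoking, drinking, cannabis use and bullying are behaviours that classmates plausibly share. The article itself warns, under Study design, that variability in individual outcomes may reflect higher-level processes.

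A school random effect cannot absorb class clustering for a comparison made within schools. If track or grade is constant within class, a two-level model counts every student as an independent observation on that factor. In effect there are far fewer, because whole classes fall on one side of the comparison. The same holds for a sub-group analysis that asks whether the programme works differently by track or grade. Confidence intervals would be too narrow and false positives too frequent, across a long list of outcomes.

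**Working it through.** **The plan's own figure.** The article states "for multiple regression analyses 15 persons/observations per parameter are to be included in the measurements for conservative power calculations" and "a sample size of approximately 500 observations is required for a power of 0.80 at an alpha-level of 0.05 for statistical significance". With 30 parameters, 15 × 30 = 450; allowing for 90% response, 450 / 0.90 = 500. The figure reproduces. It contains no clustering term, so it gives no information on class or school correlation.

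**Inputs.** From the article: 4 schools, 2 per arm, about 1500 students, alpha 0.05. Assumed, because the article gives none: 15 classes of 25 per school (4 × 15 × 25 = 1500), class ICC 0.02 to 0.10, school ICC 0 to 0.03, and track or grade constant within class. Total variance is set to 1.

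**1. A factor that varies between classes.** Design effect DE = 1 + (25 − 1) × ICC. The SE is too small by √DE. The actual size of a two-sided 5% test is 2 × [1 − Φ(1.96/√DE)].

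| Class ICC | DE | √DE | Actual size |
|---|---|---|---|
| 0.02 | 1.48 | 1.22 | 10.7% |
| 0.05 | 2.20 | 1.48 | 18.6% |
| 0.10 | 3.40 | 1.84 | 28.8% |

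With 20 students per class the sizes are 9.5%, 16.0% and 25.0%; with 30 they are 11.9%, 21.0% and 32.1%. Simulation (5,000 datasets per setting, 5 classes against 10 in each school) agrees. At class ICC 0.05 and school ICC 0, the two-level SE is 0.055 against a true 0.080, with 19.1% rejection. An arm-by-track interaction carries the same inflation, since it too compares means of whole classes.

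**2. A factor balanced within classes, such as gender.** Class effects cancel in the contrast. At class ICC 0.05 the two-level SE is 0.0516 against a true 0.0502 (4.3% rejection). At 0.10 it is 0.0515 against 0.0483 (3.7%). The test is slightly conservative.

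**3. The overall arm effect.** With n = 375 per school and m = 25 per class, the true variance of the arm difference is (n × school variance + m × class variance + residual variance) / n.

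- *School ICC 0, class ICC 0.05.* The variance is (0 + 1.25 + 0.95)/375, so the SE is 0.077. Over all runs, the root-mean-square two-level SE is 0.080, because the estimated school variance absorbs the class variance. In 37% of runs the school variance is estimated at zero. In those runs the two-level SE is 0.052 against a true 0.076, rejection is 18.5%, and a class level restores the SE to 0.075.
- *School ICC 0.01, class ICC 0.05.* The variance is (3.75 + 1.25 + 0.94)/375, so the SE is 0.126. In the 16% of runs with a zero estimate, the two-level SE is 0.051 against a true 0.125, and a class level gives only 0.075.

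Type I error for the arm effect over all runs, from larger simulations of the same layout (at least 40,000 datasets per setting):

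| School ICC | Class ICC | Reference | Two-level | Three-level |
|---|---|---|---|---|
| 0 | 0.05 | Wald-z | 10.1% | 4.2% |
| 0 | 0.05 | Satterthwaite | 6.6% | 3.2% |
| 0.02 | 0.02–0.10 | Wald-z | 17–18% | 13–16% |
| 0.02 | 0.02–0.10 | Satterthwaite | 6.3–6.5% | 7.0–7.3% |

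**The case against.** The strongest reply is that allocation is by school and the model contains that level, so the main comparison is already covered. For the arm effect this largely stands. A reader might infer that leaving out class invalidates the arm comparison and that a third level would repair it. The figures do not support that. At school ICC 0.02 the three-level model still rejects 13–16% with Wald-z, and with Satterthwaite degrees of freedom it does no better than the two-level model. Adding class also makes a zero estimate of school variance more frequent: 15–63% of runs against 9–49%. With a fixed 2-degree-of-freedom reference, two-level rejection is at most 3.2% in every setting tried. The article names no degrees-of-freedom method, so the Wald-z figures are conditional. The case in which omitting class does matter needs almost no true variation between four separate schools.

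A reader might also infer that every within-school or sub-group effect is affected. That is not so. Gender is not, and Table 1 also lists ethnicity, family affluence and age, which nothing in the article makes constant within class.

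A third tempting inference is that class will not be recorded, because Table 1 omits it. Table 1 also omits grade, survey year and any student identifier, so the omission shows nothing either way.

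Three further points stand as limits. The article announces no specific test of track or grade. Class size and both ICCs are assumed. The simulation is an unadjusted cross-section, while the plan analyses change, and baseline adjustment may lower the residual class correlation. The study is also exploratory. None of this removes the point: the article fixes two levels, records track, surveys three grades and intends sub-group analyses.

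**Conclusion.** The point holds in a limited form. The two-level model understates standard errors for effects that vary mainly between classes, if outcomes correlate within class. The inflation of a nominal 5% test to about 11%, 19% or 29% rests on 25 students per class, class ICC 0.02, 0.05 or 0.10, and track or grade being constant within class. It would be smaller with lower residual correlation, and absent if there is none.

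For the overall arm effect, class matters only when the school variance is both estimated at zero and truly near zero. Beyond that, the limitation is the number of schools. The change is worth making because it is cheap and because track and grade are natural sub-group factors here.

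**What to change.** Make sure a class identifier is recorded with each in-class questionnaire in every annual round; under confidential survey procedures it may be hard to reconstruct later. Add a class random effect (student, class, school) to the multilevel models, at least to those estimating track, grade or related sub-group effects.

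As a separate step, keep the school random effect and state small-sample degrees of freedom for the arm contrast. The class level should not be presented as a remedy for having four schools.

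The cost is one extra survey field, one extra variance component and somewhat wider intervals. If class variance proves negligible, the results will change little.
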